### Randomization

After written consent is obtained, patient/family dyads will be randomly assigned to one of the two study arms, the: (1) intervention or (2) usual transitional care management arm. Dyads will be randomly assigned to one of the two study arms, with stratification based on TBI severity. Due to the nature of the intervention, the participants, interventionists, and the investigators responsible for overseeing the BETTER intervention cannot be blind to the allocation of participants to each group.

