### Data analysis

For Aim 1, a descriptive analysis will be initially performed by examining distributional properties of demographic and clinical variables both for the overall sample size, as well as stratified by whether the individual received BETTER or usual transitional care management. Similarly, data will be stratified by (1) primary language spoken, (2) racial/ethnic group, and (3) sex to ensure randomization was successful. Differences in categorical explanatory variables will be tested using chi-square techniques (or the Fisher Exact test, when appropriate); while differences in continuous explanatory variables will be tested using independent-samples t-tests (or ANOVA, when appropriate).

The effects of the two arms (treatment vs. usual transitional care management) on the primary outcome in this RCT will be estimated and compared using repeated measures ANOVA to support the central hypothesis that adults with TBI receiving BETTER will have higher QOL 16-weeks after hospital discharge than those receiving usual transitional care management. Similarly, for our secondary aims, we will further examine if such differences exist in SF-36 total scores between these groups, over time by (1) primary language spoken, (2) racial/ethnic group, and (3) sex. The primary analytic endpoint for Aim 1 is at 16-weeks post-discharge to assess the longevity and efficacy of our observed effects, consistent with previous literature.

The longitudinal design of this study also allows us to examine if effects are observed as early as 8-weeks post-discharge; and whether effects hold (or are further increased) at 16- and 24-weeks post-discharge. Thus, linear mixed-effects models (LMMs) will be conducted. The two arms (BETTER vs. usual transitional care management), will be analyzed as fixed effects and time will be analyzed as a repeated measures effect to examine whether these outcomes significantly change over time. Other main effects (primary language spoken, race/ethnicity, sex) will be incorporated as covariates during secondary analyses. All main effects and all interactions will be investigated for significance from the mixed-effects models.

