### Sample size determination

Findings from the pilot study were combined with literature on the clinically meaningful difference in SF-36 total scores for patients with TBI between groups (0.3 standard deviations) to perform the power analysis for this study.[32, 87] For this study, a total of N = 356 individuals will provide 80% power for the study design described above (α = 0.05, two-tailed) to detect a small effect size between study arms (Cohen’s d = 0.18). A sample size of N = 356 represents 178 patient/family dyads with 89 dyads randomly assigned to the treatment arm and 89 dyads randomly assigned to the usual transitional care management arm. Based on our preliminary studies, we anticipate that 10% of eligible participants will decline participation and that 10% of recruited/enrolled participants will be lost to follow-up.[32] As such, to account for attrition, our enrollment goal is N = 436 individuals (218 patient/family dyads; 109 dyads per arm). It worth noting that the power calculations were performed only for the primary outcome, patient QOL changes in SF-36 total scores from baseline to 16 weeks post-hospital discharge, to test our central hypothesis. We powered this study to detect a small effect size to ensure we can detect the minimal clinically important difference.^31^

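### The primary comparison names no adjustment for baseline SF-36 or for the TBI-severity randomisation stratum, and the endpoint is worded both as 16-week level and as change

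*Protocol article*

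**What the plan says.** Under Randomization, dyads are allocated "with stratification based on TBI severity". Under Data analysis, the primary outcome is compared between arms by repeated measures ANOVA, in support of the hypothesis that "adults with TBI receiving BETTER will have higher QOL 16-weeks after hospital discharge than those receiving usual transitional care management". Linear mixed models then examine 8, 16 and 24 weeks, with arm as a fixed effect and time as a repeated-measures effect. The only covariate statement in the efficacy analysis follows: "Other main effects (primary language spoken, race/ethnicity, sex) will be incorporated as covariates during secondary analyses". TBI severity is not among them, and baseline SF-36 is not named as a covariate anywhere.

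The abstract, the introduction and Data analysis express the endpoint as quality of life at 16 weeks. Data collection calls the primary outcome the change in SF-36 total score, and Sample size determination says that the power calculation was for "patient QOL changes in SF-36 total scores from baseline to 16 weeks post-hospital discharge".

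Table 1 schedules the SF-36 before discharge and at 8, 16 and 24 weeks. Data collection expects baseline data from 100% of dyads and 16-week data from 80%.

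**The concern.** Two kinds of information are available before treatment can act: the patient's baseline SF-36 and the stratum within which the patient was randomised. Putting both in the primary model is standard and takes no extra data. A comparison that uses neither as a covariate has a larger standard error than it needs.

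The level and the change score share an expected arm difference under randomisation, but as unadjusted statistics they have different variances and will give different estimates and p-values in the actual data. Participants, interventionists and the investigators overseeing the intervention are not blinded, so the primary contrast should be fixed in advance and unambiguous.

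**Working it through.** **The plan's own figure.** Sample size determination states that "a total of N = 356 individuals will provide 80% power for the study design described above (α = 0.05, two-tailed"), with 89 patients per arm providing an SF-36 score, "to detect a small effect size between study arms (Cohen’s d = 0.18"). A two-sample comparison at d = 0.18 and two-sided 5% needs about 485 patients per arm. With 89 per arm the power is about 22%, and with 178 per arm about 40%. The stated 80% is therefore not reproduced by a simple comparison of patients. Some repeated-measures calculations come near 178 patients, but only with correlations (and in one case an effect measure) that the document does not state. That is a separate problem. It matters here because this calculation gives no correlation or covariate assumption to carry forward.

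**Inputs for the precision check.**
- Patients per arm at 16 weeks: 109 enrolled (Sample size determination) × 0.80 (Data collection) = 87.2, taken as 87.
- Difference: 0.3 SD, the value that Sample size determination calls clinically meaningful.
- Two-sided α = 0.05.
- Correlation r between baseline and 16-week SF-36: not given. Assumed 0.3, 0.5 and 0.7, with equal SDs at the two visits.

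**Formulas.** Relative to the variance of the 16-week level:
- level: 1
- change from baseline: 2(1 − r)
- baseline-adjusted (ANCOVA): 1 − r²

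The ratio of adjusted to change is (1 − r²) / [2(1 − r)] = (1 + r)/2, so the variance saved against change is (1 − r)/2. Power comes from the noncentral t with 87 per arm and standardised effect 0.3/√(variance factor).

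| r | Change factor | Adjusted factor | Adjusted ÷ change | Variance saved vs change | Power, change | Power, level | Power, adjusted |
|---|---|---|---|---|---|---|---|
| 0.3 | 1.40 | 0.91 | 0.65 | 35% | 38% | 50% | 54% |
| 0.5 | 1.00 | 0.75 | 0.75 | 25% | 50% | 50% | 62% |
| 0.7 | 0.60 | 0.51 | 0.85 | 15% | 72% | 50% | 79% |

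The change score beats the level only when r exceeds 0.5. Apart from a negligible loss of degrees of freedom, the adjusted estimate is never less precise than either.

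**The stratum.** The document does not say how much SF-36 variance severity explains. Assume 2%, 5% or 10% (R²). Dividing 0.3 by √(1 − R²) moves the power of the level comparison from 50% to 51%, 52% or 55%. If the stratum is balanced by design and then ignored, the true two-sided error is 2[1 − Φ(1.96/√(1 − R²))] = 0.048, 0.044 or 0.039. The test stays valid and is slightly conservative.

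**The case against.** The strongest reply is that this is a condensed article whose analysis plan is not shown, and that covariates and the coding of baseline usually sit there. The covariate sentence belongs to the mixed-model paragraph and bears on the primary comparison only by exclusion. A mixed model with a common baseline mean would recover essentially the same gain, and nothing in the article rules one out. This has weight, but the article does more than stay silent: it names the primary method, lists covariates, places them in secondary analyses, and leaves out the one variable used to stratify. It also states the endpoint in two ways. Those are points in the text as written.

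Three stronger readings are tempting, and the document does not support them.

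- *Baseline SF-36 is left out of the primary analysis.* It is a scheduled assessment, Data collection says that all outcome data will be used, and a change score contains it by construction. What is missing is its use as a covariate, and a statement of whether it is a level of the time factor. If it is, the arm-by-time contrast is a change comparison, and the loss is (1 − r)/2 of that variance rather than the full r² lost by ignoring baseline.
- *The switch between level and change itself costs precision.* It does not. It is an inconsistency of definition; any cost depends on which version is run and on r.
- *Ignoring the stratum makes the test invalid or badly underpowered.* The test is valid, and the loss is probably small.

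It is also fair that the power figures describe simple two-visit tests. The planned analysis uses up to four visits, and its precision depends on a covariance structure that the article does not give.

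**Conclusion.** The point holds as a worthwhile improvement in method together with a wording inconsistency; it is not an error that invalidates the trial. As stated, the primary comparison adjusts for neither baseline SF-36 nor the severity stratum, and the endpoint is defined in two ways.

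At 0.3 SD with 87 patients per arm, baseline adjustment gains about 16, 12 and 7 percentage points of power over the change score at r = 0.3, 0.5 and 0.7. Over the unadjusted level it gains about 4, 12 and 28 points. The direction of the gain does not depend on r; its size does, and it also rests on equal SDs and a two-visit comparison. The contribution of the stratum cannot be derived from the document.

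Adjustment does not rescue the sample size: at d = 0.18 with 89 per arm, r would have to be about 0.90 to reach 80% power.

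**What to change.** Define the primary estimate as the adjusted mean difference between arms in SF-36 total score at 16 weeks. Obtain it from a repeated-measures mixed model of the post-discharge visits with terms for arm, visit, arm-by-visit, baseline SF-36, baseline-by-visit and the TBI-severity randomisation stratum. Report change from baseline descriptively. Align Data collection, Data analysis and Sample size determination with this one definition, and say that baseline is a covariate and not a level of the time factor. With baseline as a covariate, level and change give the same treatment estimate, so the ambiguity disappears.

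The cost is a few sentences in the protocol and analysis plan and a few degrees of freedom. Baseline SF-36 and TBI severity are already collected. The basis of the sample size needs its own correction.

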## Methods

### Study design

This will be a single-site, two-arm, randomized controlled trial of BETTER, a culturally- and linguistically-tailored, patient- and family-centered, behavioral, TBI transitional care intervention for diverse English- and Spanish-speaking patients with TBI and their families, compared to usual transitional care management. In addition to baseline assessments at 24–72 hours pre-hospital discharge for both groups, follow-up assessments will occur at 8-weeks, 16-weeks, and 24-weeks post-discharge from acute hospital care to home. Dyads in both the treatment and usual transitional care management arms will complete the same data collection measures at the same time points to allow for comparison in the longitudinal analyses (see **Fig 1** for SPIRIT schedule of enrollment, intervention, and assessments). The study design of the BETTER RCT is illustrated in detail (see **Fig 2** for RCT design). The RCT is registered with clinicaltrials.gov (NCT05929833) and is funded by the National Institutes of Health (Grant # R01NR020818).

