### Sample

Patients with TBI of any race/ethnicity, regardless of insurance status, will be eligible if they are: a) age ≥18 years; b) diagnosed with mild, moderate, or severe TBI [admission Glasgow Coma Scale score of 3–15];[50] c) admitted to an inpatient acute care unit; d) to be discharged directly home from the acute hospital without inpatient rehabilitation or transfer to other settings (community discharge); e) sufficient cognitive functioning to participate (i.e., able to follow 2-step commands), as determined by the Galveston Orientation and Amnesia Test (score ≥76 eligible);[51] f) English- or Spanish-speaking (self-report), and g) access to a phone or computer with internet capabilities for study participation. Patients with TBI will be excluded if they have: a) pre-injury cognitive impairments, early dementia, or Alzheimer’s disease, b) acute, unstable neurologic condition(s), c) severe psychiatric diagnosis that is untreated with no psychiatric provider on record, d) been admitted from settings or locations other than home, or e) not been able to identify a family member to participate with them in the study.

Family members will include patient-identified biological relatives and friends [52] and are eligible if they: a) are an anticipated primary caregiver after discharge (i.e., plans to live in same home as patient *or* have direct contact with patient ≥10 hours/week);[53] b) age ≥18 years; c) English- or Spanish-speaking (self-report), and d) access to a phone or computer with internet capabilities for study participation. Family members will be excluded if the associated patient is not eligible or declines participation. All participants must be able to consent to participate. Patients and their associated family caregiver will be recruited.

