For all the analyses, intent-to-treat approach will be adopted as pre-planned for main effect comparisons between (1) BETTER vs. usual transitional care management, (2) primary language spoken, (3) racial/ethnic group, and (4) sex. Also, the bootstrap interval estimates will be generated for comparisons in all the linear models when model assumptions are untenable.

For Aim 2, interview transcripts will be coded using conventional content analysis, a data analysis technique suitable in an area where little is known.[85] The qualitative team is well-versed in qualitative methods and will consist of three bilingual members. The team will first read through all translated transcripts to get a holistic sense of the data and write memos describing initial impressions.[85] The team will then independently code transcripts and meet to discuss and compare codes and reach consensus on discrepancies. Codes will be entered into a codebook, with code names and definitions and quotation exemplars. The codebook will evolve as coding continues. Similar codes will be grouped into themes.[85] Findings will be reported using thick description and quotation exemplars as evidence of findings. Several strategies will be utilized to increase trustworthiness and rigor of findings, including developing an audit trail, engaging in peer debriefing, and including detailed methods and context of our sample and data collection and analytical procedures in publications and presentations describing findings.[86]

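### Testing every main effect and interaction of arm, time, language, race/ethnicity and sex for significance gives about a coin-flip chance of a false arm-by-subgroup signal and little power to find a real one

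*Protocol article*

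**What the plan says.** The Data analysis section compares the arms on the primary outcome by repeated measures ANOVA, with 16 weeks as the primary endpoint. For the secondary aims it adds that "we will further examine if such differences exist in SF-36 total scores between these groups, over time by (1) primary language spoken", and goes on to racial/ethnic group and sex.

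It then describes linear mixed-effects models to show whether effects appear at 8 weeks and persist. In these the arms "will be analyzed as fixed effects and time will be analyzed as a repeated measures effect". Of the remaining factors it says "Other main effects (primary language spoken, race/ethnicity, sex) will be incorporated as covariates during secondary analyses". The rule at issue follows: "All main effects and all interactions will be investigated for significance from the mixed-effects models". The article sets no limit on the order of interaction, no ranking of tests and no exploratory label.

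The next paragraph says that an "intent-to-treat approach will be adopted as pre-planned for main effect comparisons between" four groupings: arm, language, racial/ethnic group and sex.

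Sample size determination states that power was calculated for the primary outcome only.

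**The concern.** Significance is the stated yardstick for every term, so the number of tests is set by the number of factors and not by the questions the trial wants answered. With five factors that number is large, and many of the terms could be reported as differential benefit of BETTER by language, ethnicity or sex. Health equity is a declared purpose in the Discussion, so such findings would attract attention. The trial was not sized for any of them. A significant term could easily be chance, and a non-significant one would say little about whether benefit is similar across groups.

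There are two further points. A full factorial also includes terms that combine language with race/ethnicity, two characteristics likely to overlap. And the intention-to-treat label is attached to comparisons of language, ethnic and sex groups, which are not created by randomisation; under Randomization, dyads are allocated only to arm, stratified by TBI severity.

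**Working it through.** **The plan's own figure.** The article gives no error rate or power for interactions. Its only power statement (356 individuals, 80% power, d = 0.18, two-sided 0.05) concerns the primary outcome. It does not reproduce directly: a plain two-group comparison at d = 0.18 has power 0.22 with 89 per arm and 0.40 with 178 per arm. That is a separate matter, and nothing below uses it.

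**Inputs**
- Arm: 2 levels. Time: 4 levels, baseline plus three visits (Study design: "follow-up assessments will occur at 8-weeks, 16-weeks, and 24-weeks post-discharge from acute hospital care to home").
- Language: 2 levels (Sample: "English- or Spanish-speaking (self-report), and g) access to a phone or computer with internet capabilities for study participation"). Sex: 2 levels.
- Race/ethnicity: number of categories not stated (Sample: "Patients with TBI of any race/ethnicity, regardless of insurance status, will be eligible"). Assumed 3, range 2 to 5.
- SF-36 is completed by patients only, so there are 218 analysis units, 109 per arm (Sample size determination). Data are expected from 80% at 16 weeks and 65% at 24 weeks (Data collection).
- Clinically meaningful difference: 0.3 SD (Sample size determination).

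**Count of terms**
- All terms: 2^5 − 1 = 31, made up of 5 main effects and 26 interactions.
- Interactions containing arm: 2^4 − 1 = 15.
- Less arm by time, which is a planned contrast and not a subgroup effect: 14 arm-by-subgroup terms.

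**False positives**, each term tested once at 0.05, none real, independence assumed: P(at least one) = 1 − 0.95^k.
- k = 14: 0.512, with 14 × 0.05 = 0.70 expected.
- k = 6 (only arm by subgroup and arm by time by subgroup, one subgroup factor at a time): 0.265.
- k = 3 (three prespecified contrasts): 0.143; at most 0.05 if each is tested at 0.05/3 = 0.0167.

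Independence is a fair approximation. A null simulation of the model without time gave 0.309 against 0.302 for 7 arm-by-subgroup terms, and 0.539 against 0.537 for all 15 terms.

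**Power for one two-group arm-by-subgroup difference of 0.3 SD.** With N patients, equal arms and a subgroup share p, each arm has Np/2 patients in one subgroup and N(1 − p)/2 in the other. So SE = √(4/(Np) + 4/(N(1 − p))) in SD units, and power ≈ Φ(0.3/SE − 1.96).
- N = 218, p = 0.5: SE = 0.271, power 0.20. Smallest difference detectable with 80% power: 2.80 × 0.271 = 0.76 SD.
- N = 174 (87 per arm, 80% of 218), p = 0.5: SE = 0.303, power 0.17.
- N = 218, p = 0.2: SE = 0.339, power 0.14. Smallest detectable difference: 0.95 SD.

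**Size of the full model**
- Fixed-effect parameters with 3 race/ethnicity groups: 2 × 4 × 2 × 3 × 2 = 96 (64 to 160 for 2 to 5 groups).
- Between-patient cells: 2 × 2 × 3 × 2 = 24 (16 to 40).
- Mean patients per cell: 218/24 = 9.1 (13.6 down to 5.5 over the range); 174/24 = 7.3 with 16-week data.

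**Empty cells**, simulated with 218 patients, 3 race/ethnicity groups and an assumed 65/35 sex split:

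| Assumed composition | Mean empty cells of 24 | P(any empty) | Parameters lost of 96 |
|---|---|---|---|
| Half of Latino patients speak Spanish, no others | 8.1 | 1.00 | 32 |
| Half of Latino patients, 2% of others | 5.3 | 1.00 | 21 |
| Language independent of ethnicity, equal groups, 20% Spanish | 0.5 | 0.42 | 2 |
| Language independent of ethnicity, equal groups, 50% Spanish | 0.02 | 0.02 | 0.1 |

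In the first row, 2 arms × 2 other ethnic groups × 2 sexes = 8 cells are empty by construction.

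**The case against.** The strongest reply is that these analyses are secondary. The article says so, keeps the primary test separate and discloses that only the primary outcome was powered. Multiplicity handling for secondary models commonly sits in an analysis plan, and this is a condensed article. All of that stands, and the absence of an adjustment is not the point made here. The point is the printed rule: testing all interactions for significance is a stated choice, and an analysis plan would have to undo it.

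One could read the sentence as covering only arm by time, with the other factors as simple covariates. That fits poorly with the words used and with the stated wish to compare arms over time by language, ethnicity and sex.

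Three stronger readings are tempting but not supported:
- A reader might infer that 218 patients cannot estimate the requested terms. The article gives neither the number of ethnic categories nor the overlap with language, and the chance of an empty cell runs from about 2% to 100% over the assumptions tried. Two-way terms are estimable.
- A reader might quote 54% (15 terms) or 74% (26 interactions) as the chance of a false subgroup claim. The first counts arm by time. The second adds 11 interactions without arm, which cannot yield a claim about BETTER.
- A reader might infer that the investigators will take non-significance as equal benefit. Nothing in the article says so; it is a risk of the method, not a stated intention.

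The intention-to-treat wording can be read as merely naming the analysis set. It is a labelling point without a numerical consequence.

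**Conclusion.** The concern holds for the rule as printed. Across the 14 arm-by-subgroup terms, the chance of at least one false signal is about 51%, assuming near-independent tests at 0.05 with no true effects. Power for a real 0.3 SD difference is about 17–20% with equal subgroups and about 14% with a 20/80 split. These power figures take the difference in SD units of the analysed outcome, without a gain from baseline adjustment. Significance would therefore be a poor guide in either direction.

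Non-estimability is conditional. It is probable for the higher-order terms, chiefly those combining language with race/ethnicity, if Spanish speakers are concentrated in one ethnic group. Otherwise it may be slight.

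It might be inferred that the trial's main result is at risk. It is not: the error rate of the primary 16-week arm comparison is untouched. The sentence should be changed, but it does not threaten the primary conclusion.

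**What to change.** Replace the sentence on all main effects and all interactions with the following:
- Keep arm by time in the longitudinal mixed model, as planned.
- Prespecify three arm-by-subgroup contrasts at 16 weeks: language, race/ethnicity (with its categories named in advance) and sex. Add each singly to the longitudinal mixed model. Interactions with time that are needed only to form the 16-week contrast are not tested separately.
- Report the arm effect within each subgroup and the difference between subgroups, with 95% confidence intervals, labelled exploratory.
- Fit no interactions that combine two or more of the subgroup factors, and draw no conclusion of equal or unequal benefit from p-values.
- In the intention-to-treat paragraph, keep that label for the arm comparison and describe outcome differences between language, race/ethnicity and sex groups as observational.

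If the three contrasts are tested at 0.05, the chance of a false signal is about 14%; with Bonferroni it is at most 5%. The cost is wording only: no change to sample size, data collection or the primary repeated measures ANOVA. What is given up is unplanned high-order exploration, for which the trial has little information anyway.
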